**4. OUTCOME MEASURES**

This study aims to evaluate the validity of objective para-clinical assessments (electrophysiological and radiological) in measuring the symptom impact of SCD. This objective is based on the correlation of clinical indicators of symptom severity with para-clinical indicators in a construct validation approach according to the hypotheses described in section 2.2, with:

- convergent validity, by verifying positive correlations between symptom impact and electrophysiological or radiological measurements on the pathological side,
- discriminant validity (or divergent validity), by verifying the absence of correlation between symptom impact and electrophysiological or radiological measurements on the healthy side.

All clinical and para-clinical measurements are detailed below, before presenting the validity and reliability outcome criteria for:

- the validity of EcoG and other objective para-clinical assessments (temporal bone CT, PEMV, WBT),
- the reliability of electrophysiological assessments (EcoG, PEMV, WBT),
- the psychometric properties of the Naert questionnaire translated into French.

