**4.2.1.3. PEMV**
Two ocular and cervical PEMV recordings are performed at each of the three visits, collecting the PEMV threshold (dB SPL) and wave amplitude characterization relative to the contralateral healthy side (absent, normal, or abnormally large). PEMV thresholds and the proportion of abnormally large PEMV across the 6 measurements are recorded.

All recordings are performed by the same examiner within one center using the EcoG module of the Eclipse® system (Interacoustics®).

In each center, the examiner responsible for electrophysiological assessments will have received standardized training by [name] (Associate Professor, University Clermont-Auvergne, and consultant to Interacoustics®).

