**4.3. OUTCOME MEASURES: VALIDITY AND RELIABILITY INDICATORS**

**4.3.1. VALIDITY**
Main indicators for evaluating convergent and discriminant validity of electrophysiological or radiological parameters relative to clinical parameters will be Pearson correlation coefficients (or standardized regression coefficients). According to the pathophysiological hypotheses in section 2.2, we expect:

- Significant positive correlation between the SP/AP ratio in EcoG and severity of each cardinal symptom measured on the corresponding VAS.
- Higher correlation between the pathological-side SP/AP ratio and each cardinal symptom than between SCD anatomical size and surface, proportion of 1 kHz absorbance peaks in WBT, or PEMV alteration and symptom severity measured on the corresponding VAS.
- No correlation between cardinal symptom severity and electrophysiological (or radiological) indicators on the healthy side.
- Moderate correlation between anatomical SCD measurements on CT and PEMV alteration or WBT 1 kHz absorbance peak presence.

Correlation coefficients will also be calculated between combined electrophysiological criteria (EcoG +/- WBT +/- PEMV) and each cardinal symptom severity, between electrophysiological criteria and generic quality of life (EQ-5D-5L), and between electrophysiological criteria and symptom severity on the French Naert questionnaire.

Patient profiles with unilateral SCD will be determined using principal component analysis, supplemented by supervised modeling.

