**6. ELIGIBILITY CRITERIA**

**6.1. INCLUSION CRITERIA**

- Unilateral SCD formally diagnosed by high-resolution CT (≤0.5 mm slices, reconstructions in the plane of the superior semicircular canal and perpendicular plane) of the temporal bone, with no requirement for symptom severity.
- If present, SCD-related symptoms must be stable in a diagnostic and follow-up context, with no therapeutic intervention planned within 3 months of the first visit.
- Adult patient (≥18 years), able to read and understand French.
- Affiliated with or beneficiary of a social security scheme.
- Free, informed, written consent signed by the participant and investigator (at the latest on the day of inclusion and before any study-related examination).

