**11. STATISTICAL ASPECTS**

**11.1. SAMPLE SIZE CALCULATION**
To evaluate reliability and validity of electrophysiological indicators, the sample size was defined to estimate reliability and validity parameters with sufficient precision.

100 patients with 6 repeated measurements will allow estimation of an intraclass correlation coefficient (ICC) > 0.80 with 95% CI width < 0.10.

Additionally, 100 patients allow the following precision for correlation values:

- 95% CI width < 0.30 for Pearson correlation ≥ 0.50
- 95% CI width < 0.40 for Pearson correlation = 0

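### Discriminant validity is defined as absence of correlation on the healthy side, with no bound and no comparison of the two sides; N = 100 cannot show absence, and the healthy-side CT correlation cannot be computed

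*Protocol*

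**What the plan says.** Section 4 sets out a construct validation in two parts. Convergent validity is a positive correlation between symptoms and measurements on the diseased side. Discriminant validity is "verifying the absence of correlation between symptom impact and electrophysiological or radiological measurements on the healthy side".

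Section 4.3.1 names Pearson coefficients (or standardized regression coefficients) as the main indicators and then lists what is expected:
- "Significant positive correlation between the SP/AP ratio in EcoG and severity of each cardinal symptom measured on the corresponding VAS"
- "No correlation between cardinal symptom severity and electrophysiological (or radiological) indicators on the healthy side"

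Section 11.2 says the divergent analysis repeats, on the healthy side, the correlations done for the electrophysiological indicators on the dehiscence side. The endpoint line in the research summary sets the affected side against the healthy side but names no comparison statistic. Section 11.1 justifies 100 patients by precision: "95% CI width < 0.30 for Pearson correlation ≥ 0.50" and "95% CI width < 0.40 for Pearson correlation = 0".

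Three further places bear on what can be computed:
- Section 6.1 requires "Unilateral SCD formally diagnosed by high-resolution CT", and section 6.2 excludes bilateral disease.
- Section 4.2.2 records from CT only the location, largest dimension and surface area of the dehiscence.
- Section 4.2.1.3 records the VEMP (PEMV) threshold and a "wave amplitude characterization relative to the contralateral healthy side (absent, normal, or abnormally large".

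**The concern.** Failing to find a correlation is not the same as showing that there is none. With an interval of about ±0.20 around zero, a healthy-side correlation of a size that matters can easily go unnoticed. If a reader then contrasts a significant result on one side with a non-significant result on the other, the contrast is between two significance statements and not between two correlations. That can mislead in both directions. A marker that tracks symptoms equally in both ears can look side-specific by chance. A marker that is truly better on the diseased side can look non-specific, because the two ears of one patient are correlated and some of the signal carries over.

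Two elements of the healthy-side criterion also have no data behind them: the CT measurements and the relative VEMP amplitude grade.

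At stake is how the affected-versus-healthy contrast is interpreted. The coefficients themselves are not at risk.

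**Working it through.** **Inputs from the protocol.** N = 100 and the two interval widths (section 11.1). Both ears are measured in every patient at every visit (sections 9.3.2, 9.4, 9.5). There are four cardinal symptoms.

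**Assumptions, not in the protocol.** Two-sided alpha of 5%, suggested by the 95% intervals. Inter-ear correlation of the marker, varied from 0 to 0.6. Normally distributed data.

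**1. The protocol's precision figures.** Fisher interval: tanh(atanh(r) ± 1.96/√(N − 3)), with √97 = 9.849.
- r = 0.50: 0.337 to 0.634, width 0.2975, below 0.30 as stated.
- r = 0: −0.196 to +0.196, width 0.393, below 0.40 as stated.

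Both reproduce. The sample-size statement is not in error; the question is what it can support.

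**2. Where significance falls.** Critical r = t/√(98 + t²) with t = 1.984, which gives 0.197. An observed 0.20 has p = 0.046 and an observed 0.19 has p = 0.058. One on each side would fit both expectations on a difference of 0.01.

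**3. Can absence be shown?** A true healthy-side r of 0.20 is detected with about 51% power, so it is missed in about 49% of studies. For a formal equivalence test (two one-sided 5% tests) at true r = 0, power is 2Φ(atanh(b)·√97 − 1.645) − 1 for bound ±b:

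| Bound | Power at N = 100 | N for 80% power |
|---|---|---|
| ±0.20 | 28% | 212 |
| ±0.25 | 62% | 135 |
| ±0.30 | 84% | 93 |

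Absence can be shown at this N only against a bound near ±0.30.

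**4. The pattern read as a rule.** Trivariate normal simulation, N = 100, one symptom. The pattern is SCD-side r significant and positive, with healthy-side r not significant. The comparator is Williams' test for two dependent correlations sharing one variable.

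Non-specific marker (same true r on both sides):

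| True r, both sides | Inter-ear r | Pattern seen | Paired test finds SCD side larger |
|---|---|---|---|
| 0.20 | 0.5 | 17% | about 2.5% |
| 0.20 | 0 | 25% | about 2.5% |
| 0.30 | 0.5 | 9% | about 2.5% |
| 0.30 | 0 | 12% | about 2.5% |

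Good marker (SCD-side r = 0.50), with healthy-side r arising only by carry-over, that is 0.50 × inter-ear r:

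| Inter-ear r | Healthy r | Pattern seen | Pattern missed | Paired test finds SCD side larger |
|---|---|---|---|---|
| 0.2 | 0.10 | 84% | 16% | 94% |
| 0.4 | 0.20 | 49% | 51% | 86% |
| 0.5 | 0.25 | 29% | 71% | 80% |
| 0.6 | 0.30 | 13% | 87% | 71% |

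**5. Four symptoms.** With a true healthy-side r of 0 for all four, at least one is significant in 1 − 0.95⁴ = 18.5% of studies if the symptoms are independent. By simulation the figure is 13% to 18% as the correlation among symptoms falls from 0.7 to 0.

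**6. What cannot be computed.** The healthy ear has no dehiscence, so size and surface are zero (or absent) for all patients and location does not exist. A Pearson coefficient with a constant is 0/0. The VEMP amplitude grade takes the healthy ear as its reference, so that ear has no grade of its own. SP/AP, the WBT peak and the VEMP threshold all have healthy-ear values.

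**The case against.** The strongest reply is that the protocol contains no such rule. Section 4.3.1 presents these lines as expectations, names coefficients as the indicators, and gives no alpha. The sample size rests on interval width and not on power. The primary objective (section 3.1) concerns the association on the dehiscence side, and the primary outcome in the abstract carries no healthy-side condition. All of this stands. A reader might infer that the primary endpoint is decided by two significance tests. The documents do not say that, and the percentages in step 4 are properties of a reading, not of a prescribed procedure.

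The error rates also depend on an inter-ear correlation that the protocol does not give, and they vary widely with it. That stands too, which is why ranges are shown. Shared equipment alone is a weak argument for carry-over, since a device common to everyone is a constant; shared patient factors are the plausible route, and their size is unknown.

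A reader might also infer that the healthy-side analysis as a whole cannot be carried out. It can, for SP/AP, WBT and VEMP threshold. Section 11.2 confines the convergent and divergent analyses to electrophysiological indicators, so the impossible CT correlation appears only in sections 4 and 4.3.1.

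Finally, a bound or a paired method could be set in an analysis plan that is not shown. That is true of the method. It does not repair a protocol definition that asks for absence to be verified, or one that asks for a correlation with a quantity that does not exist.

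**Conclusion.** The concern holds in limited form. As defined, discriminant validity asks for something that 100 patients cannot show unless correlations up to about ±0.30 are accepted as none. The two sides are never compared directly, although paired data are collected.

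Read as a contrast of significance statements, the criterion would be met for a given symptom by a non-specific marker (true r = 0.20 on both sides) in about 17% to 25% of studies. It would be missed by a good marker in about 16% to 87%. These figures assume two-sided 5%, normal data and the inter-ear correlations shown.

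Separately, and without any assumption, the healthy-side radiological correlation is undefined and the relative VEMP amplitude grade has no healthy-ear value. The primary EcoG coefficients, the data collection and the sample size are unaffected. This is a cheap improvement plus one correction; it does not show that the primary analysis is invalid.

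**What to change.** In sections 4, 4.3.1 and 11.2, assess discriminant validity for each symptom by r(SCD side) − r(healthy side), with a 95% CI from a dependent-correlation method (Williams or Steiger) or a patient-level bootstrap. Report both coefficients with their own CIs alongside. If the sponsor prefers to keep absence as the claim, state the bound in advance and accept the power shown in step 3.

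In sections 4 and 4.3.1, delete the radiological element from the healthy-side criterion. For VEMP on the healthy side, use the threshold or each ear's own amplitude in place of the relative grade.

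The cost is a change of wording and one extra interval per symptom, with no new visits or measurements, because both ears are already recorded (each ear's own VEMP amplitude, if chosen, must be kept as a value). The downside is that the claim becomes a weaker correlation on the healthy side instead of none. A numerical minimum for convergent validity is optional and for the sponsor to choose.

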**4.1. CLINICAL MEASURES OF SYMPTOM SEVERITY**

**4.1.1. CARDINAL SYMPTOMS (REFERENCE MEASURES)**
Cardinal symptoms, the Naert questionnaire, and quality of life will be assessed at each visit.

**4.1.1.1. PULSATILE TINNITUS**
The presence and severity of unilateral pulsatile tinnitus on the SCD side will be assessed using a visual analog scale (VAS) ranging from 0 (no pulsatile tinnitus) to 100 (extremely disabling pulsatile tinnitus) at each of the three planned visits.

**4.1.1.2. BONE-CONDUCTED HYPERACUSIS WITH AUTOPHONY**
The presence and severity of autophony on the SCD side will be assessed using a VAS ranging from 0 (no autophony) to 100 (extremely disabling autophony) at each of the three planned visits.

**4.1.1.3. SOUND-INDUCED VERTIGO OR INSTABILITY**
The presence and severity of sound-induced balance disorders (vertigo and/or instability) will be assessed using a VAS ranging from 0 (no sound-induced balance disorder) to 100 (extremely disabling sound-induced balance disorder) at each of the three planned visits.

**4.1.1.4. PRESSURE-INDUCED VERTIGO OR INSTABILITY**
The presence and severity of pressure-induced balance disorders (vertigo and/or instability) will be assessed using a VAS ranging from 0 (no pressure-induced balance disorder) to 100 (extremely disabling pressure-induced balance disorder) at each of the three planned visits.

**4.1.2. NAERT QUESTIONNAIRE TRANSLATED INTO FRENCH**

**4.1.2.1. QUESTIONNAIRE DESCRIPTION IN ENGLISH**
The scale, in both English and translated French versions, consists of 31 items measuring the severity of 22 symptoms reported in SCD, identified from a systematic literature review (Naert et al., 2018). Responses are recorded on a 5-point Likert scale from 0 (no problem) to 4 (as severe as possible).

The original English questionnaire is reproduced below.

The Cronbach alpha coefficient was estimated at 0.969 in a sample of 29 SCD patients and 58 controls (Naert et al., 2021). The French translation method is presented in section 5, Study Design.

**4.1.3. QUALITY OF LIFE (EQ5D-5L)**
The EQ5D-5L is a generic quality-of-life questionnaire consisting of 5 questions on:

- Mobility,
- Self-care,
- Usual activities,
- Pain/discomfort,
- Anxiety/depression.

Responses use a 5-level Likert scale. A self-rated health measure is also taken using a visual analog scale (0–100): “How good or bad is your health today?”

**4.2. PARACLINICAL MEASURES**

**4.2.1. ELECTROPHYSIOLOGY**
Electrophysiological tests will be performed twice during each of the three visits, for a total of 6 measurements.

**4.2.1.1. ELECTROCOCHLEOGRAPHY**
Two EcoG measurements are performed at each of the three planned visits, recording summation potential (SP) and action potential (AP) at each measurement (see Figure 3). The SP/AP ratio is calculated for each of the 6 measurements, as well as an average SP/AP ratio per visit and an overall average across all 6 measurements.

*Figure 3: Electrode placement and typical EcoG recording (from Interacoustics Academy)*

All recordings are performed by the same examiner within one center using the EcoG module of the Eclipse® modular system by Interacoustics®.

**4.2.1.2. WIDEBAND TYMPANOMETRY (WBT)**
Two WBT recordings are performed at each of the three visits in response to wideband auditory stimulation (226–8000 Hz). They allow determination of the absorbance peak for each of the 6 measurements (see Figure 4), with the frequency of the peak recorded. The proportion of absorbance peaks at 1 kHz (associated with SCD in the literature) across the 6 measurements is also recorded.

*Figure 4: Procedure and typical 1 kHz absorbance peak in SCD (from Eberhard, 2021)*

All recordings are performed by the same examiner within one center using the Titan® tympanometry system (Interacoustics®).

**4.2.1.3. PEMV**
Two ocular and cervical PEMV recordings are performed at each of the three visits, collecting the PEMV threshold (dB SPL) and wave amplitude characterization relative to the contralateral healthy side (absent, normal, or abnormally large). PEMV thresholds and the proportion of abnormally large PEMV across the 6 measurements are recorded.

All recordings are performed by the same examiner within one center using the EcoG module of the Eclipse® system (Interacoustics®).

In each center, the examiner responsible for electrophysiological assessments will have received standardized training by [name] (Associate Professor, University Clermont-Auvergne, and consultant to Interacoustics®).

**4.2.2. CT SCAN**
Formal evidence of SCD is a main inclusion criterion. Temporal bone CT is performed before inclusion using high-resolution scans (≤0.5 mm slices), with reconstructions in the plane of the superior semicircular canal and its perpendicular plane (see Figure 5).

*Figure 5: Reconstructions of the superior semicircular canal and perpendicular plane confirming SCD*

SCD is characterized by loss of bone hyperdensity over at least two consecutive slices (Lookabaugh et al., 2015). Its location (anterior limb, arch, posterior limb), largest dimension in mm, and surface area in mm² are recorded.

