**5. STUDY DESIGN**

**5.1. JUSTIFICATION OF METHODOLOGICAL CHOICES**
In this study, the objective is to evaluate the validity and reliability of various electrophysiological parameters to better and objectively identify the severity of symptom impact in SCD.

The reliability of a measurement sets the upper limit of the maximum validity it can achieve (Streiner, 2015). The methodological choices made to address the objectives are as follows:

- Selection of patients with unilateral SCD formally diagnosed by temporal bone CT: patients with bilateral SCD will not be included to avoid uncertainty in attributing symptoms to one, the other, or both SCDs.
- No requirement for symptom severity, to obtain a population sufficiently heterogeneous in terms of symptom impact and representative of patients followed in ENT hospital services.
- Stable SCD in a diagnostic and follow-up context, with no therapeutic intervention planned within 3 months of the first visit. This allows evaluation of the test-retest reliability of different electrophysiological parameters, with measurements repeated over 3 successive visits (less than one month apart) and 2 repeated measurements at each visit. These repeated measures will allow assessment of intra-patient reliability (6 repeated measurements), intra-visit reliability (2 repeated measurements per visit), and inter-visit reliability (3 repeated visits).

The evaluation of the validity of electrophysiological measurements will primarily rely on a convergent and divergent validation approach by estimating the associations between each electrophysiological parameter and patient-reported symptoms (cardinal symptoms, Naert questionnaire, and quality of life). The main hypothesis (based on the theoretical model from the literature) is that the SP/AP ratio measured in electrocochleography will be the parameter most strongly correlated with the cardinal symptoms, compared to other electrophysiological parameters. More generally, all correlations obtained in this study between clinical and paraclinical measures will provide a better understanding of the construct validity of the various electrophysiological parameters.

The Naert questionnaire is not yet validated in French. A translation of the scale is underway, and the psychometric properties of this new translated version will be evaluated during this study. Repeated administration of the questionnaire over the 3 follow-up visits will allow assessment of test-retest reliability.

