**9.3.2. VISIT PROCEDURE**
The pre-inclusion/inclusion visit is conducted by the investigator. Before any study-related examination, the investigator obtains free, informed, written consent from the participant (or legal representative, if applicable).

At the pre-inclusion visit, the previously performed temporal bone CT will be examined to formally confirm the SCD diagnosis.

At the inclusion visit, the following will be performed:

- Clinical examination and evaluation of cardinal symptoms (pulsatile tinnitus, autophony, sound-induced balance disorders, pressure-induced balance disorders)
- Naert questionnaire
- Electrophysiological measurements recorded twice on the healthy ear and twice on the affected ear:
  - Electrocochleography (EcoG)
  - Ocular and cervical VEMP
  - Wideband tympanometry (WBT)

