**11.2. STATISTICAL METHODS**
Data will be described overall; outliers will be identified and corrected if possible. Missing data will be described for the population.

Inclusion/exclusion criteria, patient follow-up, and reasons for early withdrawal will be described, with a flow chart for inclusions and withdrawals.

Reliability of repeated measures will be evaluated first, as it allows further validity assessment:

- Electrophysiological indicators: intra-patient reproducibility (6 repeated measures), inter-visit (3 visits), intra-visit (2 measures per visit) using Bland-Altman plots (1999) with mean bias, 95% CI, and limits of agreement. Adaptation for more than 2 repeated measures will be used for inter-visit or intra-patient reliability (Jones et al., 2011). Intraclass correlation coefficients with 95% CI will also be calculated.
- The same reliability assessment applies to 3 repeated cardinal symptom measures.

If clinical and paraclinical measures are reliable, the validity of indicators will be analyzed using the mean of 6 repeated electrophysiological measures and the mean of 3 repeated clinical symptom measures.

- Convergent validity: correlations between electrophysiological indicators on the pathological (SCD) side and symptoms (presence, intensity, Naert questionnaire)
- Divergent validity: same analyses for the healthy side
- Correlations between electrophysiological indicators, anatomical-radiological measures, symptoms, and quality of life will be described to better understand construct validity.

If inter-visit reliability does not allow use of repeated-measure means, correlations may be estimated using mixed-effect models after standardization of variables. Psychometric properties of the French-translated Naert questionnaire will be assessed (inter-item correlations, item-total correlations, Cronbach’s alpha). Factor analysis will be performed.

Test-retest reproducibility of the Naert questionnaire will be evaluated by intraclass correlation coefficient and Bland-Altman indicators (3 repeated measures across 3 visits).

Unsupervised multivariate descriptive analysis (PCA, clustering) will define patient profiles based on electrophysiological, anatomical, and symptom characteristics. Supervised modeling (partial least squares regression) may also be applied to predict symptoms from multivariable indicators (+/- anatomical indicators).

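### The SP/AP-versus-CT comparison sets a mean of six readings against CT measurements whose reliability is never estimated

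*Protocol*

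**What the plan says.** **SP/AP.** Protocol 4.2.1.1 plans two electrocochleography recordings at each of three visits and an overall average. Sections 4.2.1.3 and 4.3.2 add one trained operator per centre and standardised equipment. Section 4.3.2 plans ICCs and Bland-Altman analyses, and section 11.2 analyses validity "using the mean of 6 repeated electrophysiological measures" provided the measures prove reliable. WBT and VEMP are also measured six times.

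**CT.** The scan predates inclusion. Sections 4.2.2 and 6.1 fix slice thickness and two reconstruction planes, 4.2.2 gives a rule for deciding that a dehiscence is present, and 6.2 excludes doubtful scans. For the values that enter the analysis, 4.2.2 lists "Its location (anterior limb, arch, posterior limb), largest dimension in mm, and surface area". It names no reader, number of readings or rule for measuring size and surface. At the pre-inclusion visit, "the previously performed temporal bone CT will be examined to formally confirm the SCD diagnosis" (9.3.2); this concerns diagnosis, not sizing. CT is absent from the reliability outcomes in sections 4 and 4.3.2 and from the reliability analysis in 11.2.

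**The comparison.** Section 2.2 hypothesises that symptoms are strongly associated with SP/AP and weakly or not at all with CT. The first secondary objective in 3.2 compares these associations, and 4.3.1 expects "Higher correlation between the pathological-side SP/AP ratio and each cardinal symptom than between SCD anatomical size and surface".

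**The protocol's own principle.** Section 5.1 states: "The reliability of a measurement sets the upper limit of the maximum validity it can achieve".

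**The concern.** Random error in a marker pulls its observed correlation towards zero. Averaging six readings removes much of that error from SP/AP; nothing comparable is planned for CT. By the principle in 5.1, the two coefficients then have different ceilings. Section 11.2 makes the validity analysis conditional on reliable clinical and paraclinical measures, and section 4.2 places CT among the paraclinical ones, yet CT is the only marker in the comparison that never passes through that check.

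At stake is one secondary conclusion: that electrocochleography tracks symptoms better than anatomy does. Error in CT pushes the result towards the ordering hypothesised in 2.2. A SAP cannot repair this afterwards, because a reliability estimate or a correction for attenuation needs repeat CT readings to have been collected.

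**Working it through.** **1. The plan's own precision figures (section 11.1).** These are "100 patients with 6 repeated measurements will allow estimation of an intraclass correlation coefficient (ICC) > 0.80 with 95% CI width < 0.10", "95% CI width < 0.30 for Pearson correlation ≥ 0.50" and "95% CI width < 0.40 for Pearson correlation = 0".

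- Pearson, Fisher z with standard error 1/√(100 − 3) = 1/√97: at r = 0.50 the interval is 0.337 to 0.634, width 0.297. At r = 0 it is ±0.196, width 0.393. Both agree.
- ICC, exact one-way F interval with n = 100 and six readings: width 0.101 at 0.80, 0.097 at 0.81 and 0.080 at 0.85. This agrees to rounding.

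The sample-size statement therefore stands.

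**2. Formulas for the comparison.**

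- Observed r = true r × √(reliability of the marker). Error in the symptom score scales both markers equally and drops out of their ratio.
- Reliability of a mean of k readings with independent errors = k × ICC / (1 + (k − 1) × ICC).

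**3. Assumptions.** The protocol gives no CT reliability and no expected true correlations. I assume a true r of 0.50 for both markers and a single-reading SP/AP ICC of 0.80, the lower edge of the range named in 11.1. CT reliability is varied on its own.

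Mean of six SP/AP readings: 6 × 0.80 / (1 + 5 × 0.80) = 4.80 / 5.00 = 0.96. Expected r for SP/AP: 0.50 × √0.96 = 0.490.

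| CT reliability | Expected r, CT | Gap | SP/AP larger in | SP/AP significantly larger in |
|---|---|---|---|---|
| 0.96 | 0.490 | 0 | 50% | 2.5% |
| 0.90 | 0.474 | 0.016 | 56% | 3.3% |
| 0.80 | 0.447 | 0.043 | 66% | 5.9% |
| 0.70 | 0.418 | 0.072 | 75% | 9.7% |
| 0.60 | 0.387 | 0.103 | 83% | 15.0% |

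The last two columns come from 10,000 simulated samples of 100 patients per row. They use the Williams t for two dependent correlations (one direction, nominal 2.5%), a correlation of 0.25 between the true marker values and an error-free symptom score. The test is only a yardstick; the protocol specifies none.

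**4. How far this depends on the assumptions.**

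- *Shared error within a visit.* If the two same-visit readings share all their error, k is effectively 3: 3 × 0.80 / (1 + 2 × 0.80) = 0.923, so SP/AP gives 0.50 × √0.923 = 0.480. The gaps become 0.006, 0.033, 0.062 and 0.093 at CT reliability 0.90, 0.80, 0.70 and 0.60.
- *Poor single SP/AP reading, good CT.* With SP/AP ICC 0.50 the mean of six has reliability 3.00 / 3.50 = 0.857 and r = 0.463. Against CT at 0.90 (0.474) the gap is −0.011, so the bias reverses.
- *No bias.* With SP/AP ICC 0.60 the mean of six has reliability 3.60 / 4.00 = 0.90, and CT at 0.90 gives no gap.

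**The case against.** The strongest reply is that nothing shows CT sizing to be unreliable. It is read from a fixed image, acquisition is partly standardised and doubtful scans are excluded, whereas each electrocochleogram is a new recording. At CT reliability 0.90 the gap is 0.016 at most under the assumptions above, and it can reverse. This stands: the direction of the bias is conditional. What remains is that the trial collects nothing to show which case applies.

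Second, the study is described as descriptive (5.2), is sized on interval width, and states an expectation with no superiority test. A gap of 0.04 is small beside an interval about 0.30 wide. This also stands. It limits how often chance and attenuation together would yield a firm claim, but the ordering of the coefficients is still what 3.2 and 4.3.1 set out to examine.

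Third, the mean of six is used only if reliability is acceptable, with mixed models otherwise. Those models would still use the repeated SP/AP readings, so the asymmetry remains.

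Stronger readings that a reader might infer go too far:

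- *CT is measured once, by a different reader at each site.* The centre neuroradiology teams in 6.3 and the investigator's visit in 9.3.2 make this plausible, but 4.2.2 does not say it.
- *Equal single-reading reliability.* Setting both at 0.60, 0.70 or 0.80 makes the SP/AP coefficient 22%, 15% or 10% larger with six independent readings (17%, 12% or 7% with an effective k of 3). No text supports that equality.
- *Attenuation could create the whole strong-versus-weak pattern of 2.2.* For a true r of 0.50 to appear as 0.20, CT reliability would have to be (0.20 / 0.50)² = 0.16. Only a modest spurious ordering is plausible.

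**Conclusion.** The concern holds as a conditional one. The protocol compares a marker averaged over six standardised readings with CT measurements that have no stated sizing rule, repeat reading or reliability estimate. If CT reliability is below that of the averaged SP/AP, the comparison favours SP/AP at equal true validity: 0.49 against 0.47 to 0.39 for CT reliability 0.90 to 0.60, given a true r of 0.50 for both and a single-reading SP/AP ICC of 0.80. The gap is smaller if same-visit readings share error, and is about −0.01 if CT reliability is 0.90 and the single-reading SP/AP ICC is 0.50.

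The point is confined to the CT part of one secondary comparison. A reader might infer that the primary result or the sample size is compromised; neither is, because the SP/AP-symptom correlation does not involve CT and the figures in 11.1 reproduce. The change is worth making because it is cheap and the possible bias runs towards the stated hypothesis.

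**What to change.** **Section 4.2.2.** Have the existing reader measure dimension and surface a second time on the existing scan, masked to the first values and to the symptom VAS. Use the mean of the two readings.

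**Sections 4.3.2 and 11.2.** Add CT dimension and surface to the reliability analyses, labelled as intra-reader reliability only, so that the error found is read as a lower bound on total CT error.

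**Section 11.2.** Report the SP/AP-versus-CT comparison in two further ways: with one SP/AP reading per patient (set against one CT reading, so that the numbers match), and with reliability-corrected correlations. Describe SP/AP as more strongly associated than CT only if the ordering holds in these analyses.

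**What it gains.** If all CT error were independent intra-reader error, the mean of two would have reliability 2 × R / (1 + R), where R is the single-reading value. For R = 0.80 this is 0.889, the expected CT correlation rises from 0.447 to 0.471, and the gap to 0.490 falls from 0.043 to 0.018. For R = 0.60 it is 0.75, and the gap falls from 0.103 to 0.057.

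**Cost.** A few minutes per scan, two eCRF fields and some analysis time; no new scan, staff or patients. The limitation is that same-reader repeats neither measure nor remove between-reader, between-site or acquisition error, so the corrected correlations may still under-correct CT. The report should say so.
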